## Abstract

This Randomized Controlled Trial [(RCT) aims to evaluate the effectiveness of a brief Acceptance and Commitment Therapy (ACT)-based intervention combined with treatment as usual (TAU) compared to TAU only in improving psychological conditions in a sample of adolescents with obesity (body mass index, BMI > 97th percentile for age and sex) within the context of a wider multidisciplinary rehabilitation program for weight loss. Fifty consecutive adolescents (12–17 years) of both genders with obesity will be recruited among the patients hospitalized in a clinical center for obesity rehabilitation and randomly allocated into two experimental conditions: ACT + TAU vs. TAU only. Both groups will attend a three-week in-hospital multidisciplinary rehabilitation program for weight loss. The ACT + TAU condition comprises a psychological intervention based on ACT combined with a standard psychological assessment and support to the hospitalization. The TAU comprises the standard psychological assessment and support to the hospitalization. At pre- to post-psychological intervention, participants will complete the Avoidance and Fusion Questionnaire for Youth, the Psychological Well-Being Scale, the Depression Anxiety Stress Scale, the Difficulties in Emotion Regulation Scale, and the Emotional Eating subscale of the Dutch Eating Behavior Questionnaire to assess psychological well-being as the primary outcome and experiential avoidance, psychological distress, emotional dysregulation, and emotional eating as secondary outcomes. Repeated-measures ANOVAs (2 × 2) will be conducted. The study will assess the effectiveness of a brief ACT-based intervention for adolescents with obesity in improving their psychological conditions by targeting specific core processes of the ACT framework (openness, awareness, and engagement). Future directions of the study will assess whether these psychological processes will contribute to addressing long-term weight loss.

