### 2.4. Randomization Procedure

Participants will be randomly assigned to the experimental (ACT+ TAU) or control (TAU) group. We will perform simple randomization with a 1:1 allocation ratio using the web site Randomization.com (http://www.randomization.com) (accessed on 8 June 2021). Randomization will occur after the baseline measurements in order to ensure similar baseline characteristics of groups.

Allocation concealment will be ensured, since all the patients will generate an anonymous code that will be associated with the randomization generated by the program. Researchers will be blind to the association made.

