### 2.8. Sample Size Calculation

In line with previous studies [60,61] to calculate the sample size, an a priori power analysis was carried out using the software G.Power 3.1.9.4 [62]. 

The required sample size was computed for an analysis of variance (ANOVA) with 2 groups (between variable; ACT + TAU vs. TAU) × 2 times (within variable; Time 0/Time 1). To the best of the author’s knowledge, no other similar studies are available in the literature. Therefore, the a priori effect size (Cohen’s *f*) for the global effect (groups x time) was set to 0.2 (small effect size) [63]. Moreover, the Type I error [α] probability was set to 0.05, and the power [1-β] was set to 0.95. In addition, correlation among repeated measures to 0.3 (small–moderate correlation/linear effect). Non-sphericity was assumed, and it was set to 1. Results showed that there is a more than 95% chance of correctly rejecting the null hypothesis of no significant effect of the interaction with an overall sample of 116 subjects: a minimum of 58 participants per group.

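### The abstract says 50 adolescents will be recruited, Section 2.8 requires 116, and nothing reconciles the two; at 50 the power is about 65%, not 95%

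*Protocol article*

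**What the plan says.** The abstract gives the only statement of how many participants are to be enrolled: "Fifty consecutive adolescents (12–17 years) of both genders with obesity will be recruited". The same sentence allocates these adolescents to ACT + TAU or TAU only, so 50 is the total for both arms.

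Section 2.8 derives a different total. "The required sample size was computed for an analysis of variance (ANOVA) with 2 groups" and two time points, and the Cohen's f "for the global effect (groups x time) was set to 0.2 (small effect size"). The Type I error "probability was set to 0.05, and the power [1-β] was set to 0.95". The section sets "correlation among repeated measures to 0.3 (small–moderate correlation/linear effect"), and on the sphericity correction it says "Non-sphericity was assumed, and it was set to 1". It concludes that more than 95% power is reached "with an overall sample of 116 subjects: a minimum of 58 participants per group".

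Section 2.4 adds that "We will perform simple randomization with a 1:1 allocation ratio". Section 2.2 (Participants) and Section 2.5 (Procedures) give no number. Section 2.9 removes from the analysis participants with missing data, those who do not attend each therapy session, and those who drop out. It states no expected rate.

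**The concern.** Two enrolment totals stand in one document, and the smaller is 50/116 = 43% of the larger. The total decides when recruitment stops and how a non-significant interaction is read in a trial designed to show superiority. At 116 analysed, a null result is reasonably informative about an effect of f = 0.2, because the chance of missing it is about 5%. At 50, the chance of missing the same effect is about 35%, while the article would still be claiming more than 95% power. A reader or a site member who sees only the abstract would take 50 as the plan.

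**Working it through.** **Inputs, all from Section 2.8:** f = 0.2 for the group-by-time interaction; alpha = 0.05; power 0.95; correlation between the two measurements rho = 0.3; epsilon = 1; k = 2 groups; m = 2 times. Equal arms follow the 1:1 ratio in Section 2.4.

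**Formula.** For the within-between interaction in a repeated-measures ANOVA, power comes from the noncentral F distribution with

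- lambda = f² × N × m × epsilon / (1 − rho)
- df1 = (k − 1)(m − 1) = 1
- df2 = (N − k)(m − 1) = N − 2

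**Step 1: reproduce the plan's figure.**

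- N = 116: lambda = 0.04 × 116 × 2 / 0.7 = 13.26, power 0.951.
- N = 114: power 0.947.

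The smallest even N that reaches 0.95 is therefore 116, exactly as Section 2.8 reports.

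**Step 2: the same formula at the abstract's total.**

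- N = 50: lambda = 0.04 × 50 × 2 / 0.7 = 5.71, power 0.649.

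**Step 3: cross-check on change scores.** Under this formula f = 0.2 corresponds to a between-group difference in change of 4f = 0.80 SD. The SD of change is sqrt(2 × (1 − 0.3)) = 1.183 in the same units. A normal approximation gives:

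- 58 per arm: 0.80 / (1.183 × sqrt(2/58)) = 3.64; 3.64 − 1.96 = 1.68; power 0.954.
- 25 per arm: 0.80 / (1.183 × sqrt(2/25)) = 2.39; 2.39 − 1.96 = 0.43; power 0.667.

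Both agree with the exact values to within about two percentage points.

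**Step 4: what 50 can detect.** With the other inputs unchanged, 80% power at N = 50 needs f of about 0.24, a difference in change of 4 × 0.24 = 0.96 SD. Power of 95% needs f of about 0.31. The planned value is f = 0.2, or 0.80 SD.

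**Step 5: sensitivity.**

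- Exclusions: Section 2.9 gives no rate, so the following is an assumption for illustration only. If 12% to 20% of 50 were excluded, 44 to 40 would be analysed and power would be 0.59 to 0.55.
- Correlation: with f held at 0.2, N = 50 gives 0.791 at rho = 0.5 and 0.947 at rho = 0.7. Fifty comes close to 95% only with a correlation far above the stated 0.3.

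**Step 6: can the two totals be read as compatible?** Fifty is not a per-arm number, since the fifty are themselves split between the conditions, and 2 × 50 = 100 is not 116 either. Nothing in the article describes 50 as a pilot, an interim count or a feasibility limit.

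**The case against.** The best defence is that an abstract is only a summary, whereas Section 2.8 is the reasoned derivation and expresses its result as a minimum per group. On that view 116 is the target, 50 is a slip, and nothing is underpowered. This may well be so, and it limits the point: a reader might infer that the trial will enrol 50 and is underpowered, but the article does not establish that. It does not establish the reverse either. Section 2.8 says what is required, and only the abstract says what will be recruited.

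A reader might also infer that the sample size calculation is faulty. It is not; 116 follows from the stated inputs. The defect is an inconsistency between two sections, not an error of arithmetic.

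Nor do the documents support a specific analysed number below 50. They plan exclusions but give no rate, so the 40 to 44 used above is only an illustration.

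Finally, the gap in detectable effect should not be overstated. Section 2.8 labels f = 0.2 as small, but under the formula that yields 116 it already stands for a 0.80 SD difference in change. The 0.96 SD detectable at 50 with 80% power should be read against that value, and against a plan built for 95% power.

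What survives is that the two totals cannot both be right, and that the article does not say which one holds.

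**Conclusion.** The point stands as an internal inconsistency that must be corrected. The abstract's 50 and the 116 of Section 2.8 are both totals for the whole trial, and no section reconciles them. If 116 is the target, the 95% power claim holds for 116 analysed participants and only the abstract is wrong. If 50 is the target, power for the planned effect is about 65%, some 30 percentage points below the stated figure.

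The 65% rests on the protocol's own f, alpha and correlation, on the planned 2 × 2 ANOVA, on equal arms and on complete data for all 50. It is close to a best case under those inputs, because simple randomization can leave unequal arms and Section 2.9 excludes incomplete cases.

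**What to change.** State one enrolment target, identically, in the abstract and in Section 2.8.

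- If the target is 116, correct the number in the abstract.
- If the target is 50, replace the 95% power statement in Section 2.8 with about 65% at f = 0.2 and correlation 0.3. Add that the difference in change detectable with 80% power under the planned ANOVA is about 0.96 SD (f about 0.24), against the planned 0.80 SD (f = 0.2).

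The cost is a change of wording. No participants are added beyond a number the article already gives. If 50 is the true target, the price is a less favourable but accurate power statement.

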## 1. Introduction

Obesity in childhood and adolescence is becoming a major public health concern. In this respect, recent estimates pointed out that globally, 124 million children and adolescents, aged between 5 and 19 years, were obese [1] In Europe, the prevalence of overweight and obese children and adolescents aged between 5 and 19 years is reported around 19%, with a higher prevalence in southern European countries [2].

Obesity in children and adolescents is associated with a higher risk of developing several physical and psychological problems that have an impact on their emotional development [3]. Research has reported associations between childhood and adolescent obesity and some form of psychopathology, such as depression [4], anxiety, and attention-deficit/hyperactivity disorder [5]. Children and adolescents with obesity are more likely to suffer from psychosocial disadvantages such as discrimination, social isolation, and bullying because of their weight [6,7,8,9]. Moreover, obesity in childhood and adolescence is associated with poor body image, low self-esteem [10], and low quality of life and well-being [11]. 

This evidence suggests that obesity is a complex disease that may dramatically impair psychological health, representing a risk factor for children and adolescents’ future development. This aspect calls for a better understanding of the associated risk factors and requires a multidisciplinary approach—entailing medical, nutritional, physical, and psychological components—aimed to address not only weight loss but also improving psychological conditions and treating obesity-related comorbidities [12,13]. 

The development of dysfunctional eating habits is one of the main factors linked to body weight, and it can be considered a barrier to weight loss [14,15]. Evidence from the literature suggests that unhealthy and dysfunctional eating habits could be related to a failure in emotional regulation strategies that leads individuals to eat in response to difficult emotions, as in the case of emotional eating defined as the tendency to eat in response to negative feelings [16]. 

Emotional regulation is defined as the ability to manage emotions, which means to recognize, understand, accept, and modulate flexible responses to emotions [17]. High emotion regulation allows individuals to act accordingly with personal goals, even in the presence of difficult emotions, while controlling for impulsive behaviors. On the contrary, when emotional regulation is lacking, emotional eating is undertaken to regulate difficult feelings. 

Since emotional eating was related to higher consumption of sweet and fatty food, as an attempt to regulate negative feelings, it was found to be positively associated with weight gain and obesity, both in adults [18] and in younger populations [19]. 

A theoretical model [20] for explaining disordered eating suggests that momentary stimuli such as the availability of tasty food in the environment, in combination with a modern sedentary lifestyle, accompanied by difficult emotions, can lead people to move toward behaviors perceived to increase or maintain a hedonic state of pleasure, such as eating tasty food immediately. The model also suggests that values clarity and behavioral commitment [to connect healthy eating habits to important life values], awareness [of their automatic thoughts], and distress tolerance [negative internal states] are specific self-regulation skills that can help individuals to deal with difficult emotions and control for their behaviors. Such skills are the main focus of Acceptance and Commitment Therapy. 

Acceptance and Commitment Therapy (ACT) [21] is a third-wave CBT raised in the last twenty years. ACT aims to promote psychological flexibility, which is defined as the ability to live in the “here and now” current moment consciously while implementing behaviors to live in line with one’s values. This can be seen in opposition to experiential avoidance (or psychological inflexibility), which is the attempt to avoid unpleasant internal states, such as thoughts, feelings, and bodily sensations. Psychological flexibility is an important component for health promotion [22], since it was found that it helps to commit to behaviors that are coherent with deeply held values and a life directions that a person chooses as important and meaningful in his life [23]. Concurrently, it entails staying in contact with the present moment, regardless of unpleasant internal states, such as thoughts and emotions, which are considered as a normal part of human life. By shifting the focus from efforts to change dysfunctional thoughts and feelings, in ACT, the emphasis is placed on promoting behaviors that are consistent with personal values and goals even when dysfunctional thoughts and feeling are present, by promoting acceptance and awareness of personal internal states.The promotion of psychological flexibility is based on three pillars: openness, awareness, and engagement. Openness refers to the willingness to develop an open and acceptable attitude toward one’s personal internal states such as thoughts, emotions, and bodily sensations; awareness refers to the ability to act intentionally with awareness about personal thoughts and sensations, without automatically reacting; engagement refers to engage oneself in committed behaviors related to personal values—that is, chosen life directions [24].

Several ACT-based protocols have been successfully applied to adolescents targeting a broad range of conditions, such as cystic fibrosis [25], chronic pain [26], ADHD [27], and at-risk adolescents [28]. In a pilot study conducted by Hayes, Boyd, and Sewell [29] thirty adolescents referred to a psychiatric outpatient service were randomly assigned to two conditions: in one, they received an ACT intervention; in the other, participants received a standard intervention for depression. The results showed a significant decrease in depressive symptoms in patients undergoing the ACT intervention. In a study conducted by Kemani and colleagues [30], an ACT-based intervention was applied to adolescents with chronic pain and their family members. Results showed improved acceptance of chronic pain and psychological flexibility in adolescents as well as decreased depressive symptoms in their parents. ACT has also been applied to adolescents with post-traumatic stress disorder [31], proving a reduction of symptoms after a 10-week intervention. 

Unfortunately, there are not many studies in the literature concerning the application of an ACT protocol for adolescents with overweight/obesity problems. However, evidence suggests that psychological flexibility is an important key factor of psychological health, since it allows people to engage in meaningful challenges, following a person’s self-concept and important life domains [22]. To the best of our knowledge, only one pilot study published in 2019 [32], evaluating the effectiveness of an ACT-based psychological intervention applied in combination with a 16-week lifestyle behavioral modification program in a sample of obese adolescents, was found. This study showed that the intervention was effective in promoting a reduction in BMI and an overall improvement in physical activity and psychological status of obese adolescents. Furthermore, the intervention was positively evaluated by both the adolescents and their parents who participated in the study.

Given these premises, the present study aims to evaluate the effectiveness of a brief ACT-based psychological intervention, compared to TAU in improving psychological conditions in a sample of adolescents with obesity attending a multidisciplinary rehabilitation program for weight loss. 

## 2. Materials and Methods

### 2.1. Study Design 

A superiority Randomized Controlled Trial (RCT) with parallel groups will be conducted with an ACT-based intervention plus TAU compared with TAU only for adolescents with obesity attending a multidisciplinary rehabilitation program for weight loss. 

### 2.2. Participants

Participants will be consecutively recruited at the admission to the division of Auxology, Istituto Auxologico Italiano IRCCS, Piancavallo (VB), which is located in the North-West of Italy, a specialized clinical center [i.e., third level] for weight loss and obesity rehabilitation.

Participants of both genders will be eligible for the study if they meet the following criteria: (1) aged between 12 and 17 according to the classification of the pubertal status [33]; (2) BMI > 97th centile according to age- and sex-specific Italian charts [34]; (3) Italian mother tongue; (4) written and informed consent to participate from both parents and written assent from participants. Patients will be excluded if they have any physical or psychiatric problems according to the Diagnostic and Statistical Manual of Mental Disorders (DSM-5) criteria that could compromise participation in the study. 

### 2.3. Measures

All demographical (gender, age, nationality, educational level, and family composition) and clinical data will be collected via self-report using Italian validated and widely used questionnaires. The following psychological measures will be collected pre (Time 0/week 1) and post (Time 1/week 3) psychological intervention. 

#### 2.3.1. Primary Outcomes 

Psychological Well-Being. The Psychological Well-Being Scales (PWB) [35] will be administered to assess psychological well-being. It is a self-report measure that explores six dimensions: self-acceptance, positive relationships with others, autonomy, environmental control, personal growth, and life purpose. The questionnaire consists of 18 items rated on a 4-point Likert scale ranging from 1 (“completely disagree”) to 4 (“completely agree”). The Italian version [36], assessed for Italian adolescents [37], is reported to have good psychometric properties (test–retest correlation coefficients: Self-acceptance: *r* = 0.82; Positive relationships: *r* = 0.81; Autonomy: *r* = 0.21; Environmental control: *r* = 0.31; Life purpose: *r* = 0.81; Personal growth: *r* = 0.78).

#### 2.3.2. Secondary Outcomes 

Experiential avoidance and fusion. The Avoidance and Fusion Questionnaire for Youth (AFQ-Y) [38] will be administered as a measure of experiential avoidance and fusion in adolescents. It consists of 8 items rated on a 5-point Likert scale ranging from 0 [“not at all true”] to 4 [“absolutely true”]. The Italian version [39] is reported to have moderate internal consistency (Cronbach’s alpha = 0.69) and good test–retest reliability (*r* = 0.64). 

Psychological distress. The *Depression Anxiety Stress Scale* (DASS-21) [40] will be administered as a measure of psychological distress, which is widely used in samples of adolescents [41,42]. It is a self-report instrument that measures several negative internal states: depression, anxiety, and stress. It consists of 21 items rated on a 4-point Likert scale, ranging from 0 to 3. The Italian version [43] showed good psychometric properties (Cronbach’s alpha values of subscales ranged from 0.83 to 0.91. The Cronbach’s alpha of the total score was = 0.92).

Emotional dysregulation. The Difficulties in Emotion Regulation Scale (DERS) [17] will be administered to assess difficulties in emotional dysregulation. This is a self-report questionnaire consisting of 36 items rated on a 5-point Likert scale ranging from 1 (“almost never”) to 5 (“almost always”), which explores the following subscales: non-acceptance of negative emotions, inability to undertake purposeful behavior when experiencing negative emotions, difficulty in controlling impulsive behavior when experiencing negative emotions, limited access to emotion regulation strategies that are considered effective, lack of awareness of one’s emotions, and lack of understanding of the nature of one’s emotional responses. The Italian version [44], which is widely used in samples of adolescents [45,46], is reported to have good psychometric properties (Cronbach’s alpha values ranged from 0.77 to 0.89. The Cronbach’s alpha of the total score was 0.92).

Emotional eating. The Emotional Eating subscale of the Dutch Eating Behavior Questionnaire (DEBQ) [47] will be administered to assess emotional eating. The DEBQ is a self-report questionnaire used to detect eating behaviors. The Emotional Eating subscale consists of 13 items, rated on a 5-step Likert scale ranging from 0 (“never”) to 4 (“almost always”). The Italian version [48] showed good psychometric properties (Cronbach’s alpha = 0.97). The DEBQ was chosen as a measure of emotional eating in our sample, since no other validated instruments are available, except for the DEBQ version for parents [49], which is unfortunately unsuitable for parents of our sample of hospitalized adolescents. 

### 2.4. Randomization Procedure

Participants will be randomly assigned to the experimental (ACT+ TAU) or control (TAU) group. We will perform simple randomization with a 1:1 allocation ratio using the web site Randomization.com (http://www.randomization.com) (accessed on 8 June 2021). Randomization will occur after the baseline measurements in order to ensure similar baseline characteristics of groups.

Allocation concealment will be ensured, since all the patients will generate an anonymous code that will be associated with the randomization generated by the program. Researchers will be blind to the association made.

